### Ethical standards

This study has been conducted in accordance with the protocols stated in the Declaration of Helsinki. Ethical authorization was given (21-PSI-2022). All national guidelines for data security are followed in the management of study data. Digitalized informed consent will be received from all members, and the confidentiality of all the data will be protected. The study design has been preregistered in ClinicalTrials.gov (ref: NCT05654987) following gold standards in research on cross-sectional studies, STROBE (Vandenbroucke et al., 2007).

Participation in the study can elicit changes in one’s emotional state. To address this specific problem, at the end of the survey, a list of up-to-date services and resources will be provided where the participants can obtain information and help concerning mental health services and lactation advice. In addition, contact details of the lead research team for each nation will be available if participants wish to seek out further information. On request, the researchers will provide the participants with the global results of the study.

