### Sample size

No restrictions have been put in place for participant registration. Nevertheless, the sample size was determined by taking into account the number of newborns in Ukraine. Consequently, a minimum sample size of 300 individuals will be recruited using a significance level of α-level of 0.05 and variability of 50%. It is essential to bear in mind, though, that the ongoing war situation, which includes the lack of electricity in Ukraine, the possibility of people evacuating cities, and missiles, may make it challenging to reach this sample size.

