### Procedure

Potential participants will be sought out through social media platforms (e.g., Twitter, Facebook, Instagram, LinkedIn, ResearchGate, WhatsApp), networks of educational institutions, healthcare facilities, and non-governmental organizations working in the area of perinatal mental health, policymakers, local organizations, and other stakeholders (utilizing the contacts provided by the Riseup-PPD), in addition to the personal networks of the research team members and through direct contact *via* text or email.

Participants taking part in the study will be asked to click on the website link found on the general project website^1^ in order to access the online questionnaire. They will then be presented with an electronic consent form that outlines the purpose and content of the questions, the risks and benefits, and the ethical considerations (such as voluntary participation, data confidentiality, secure storage of data, and the lack of financial compensation). At the bottom of the form, they must confirm that they meet the eligibility criteria and provide consent for the study. If a participant does not meet the criteria, they will be directed to a message thanking them for their interest and informing them of the requirements for participation. Completion of the baseline questionnaire is estimated to take around 35 min.

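### The help list meant to address distress from taking part is described only at the end of a survey of about 35 minutes, so as written it does not reach a woman who stops part-way

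*Protocol article*

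**What the plan says.** The Ethical standards section names the risk: "Participation in the study can elicit changes in one’s emotional state". The next sentence, framed as the answer to that problem, gives the remedy and its position: "at the end of the survey, a list of up-to-date services and resources will be provided". The paragraph then adds a second provision: "In addition, contact details of the lead research team for each nation will be available if participants wish to seek out further information".

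The Procedure section describes the route into the survey. A woman follows a link from the project website and sees an "electronic consent form that outlines the purpose and content of the questions, the risks and benefits". At the foot of that form she confirms eligibility and consents. If she is not eligible, the article says that "they will be directed to a message thanking them for their interest and informing them of the requirements for participation". On length it says: "Completion of the baseline questionnaire is estimated to take around 35 min".

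The Sample size section lists conditions that may hamper the study: "the lack of electricity in Ukraine, the possibility of people evacuating cities, and missiles".

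**The concern.** A remedy placed on the last page works only for women who reach the last page. Here the remedy answers a harm that can arise on any earlier page, and that harm is itself a reason to leave. A woman who closes the browser because the items on war exposure or trauma symptoms upset her has met the hazard. On the text as it stands, she has not been shown where to turn.

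What is at stake is participant protection rather than an estimate or a test. The study is online, and the article describes no staff contact while a woman fills in the questionnaire. Its Introduction also presents the population as one with a heavy burden of trauma symptoms, citing a PTSD frequency of 34.8% in internally displaced pregnant women in an earlier Ukrainian study.

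**Working it through.** The article states no figure on this point that could be reproduced, so the check is to set its statements side by side and follow a participant through them.

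**What she is asked.** The Variables and measures subsections give these item counts:

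| Instrument | Items |
|---|---|
| Study-specific questionnaire, including exposure to armed conflict | 40 |
| EPDS | 10 |
| GAD-7 | 7 |
| City Birth Trauma Scale | 29 |
| IES-R | 22 |
| TIPI | 10 |

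The sum is 40 + 10 + 7 + 29 + 22 + 10 = 118. It is 120 if the two further birth-scale questions that the article mentions are counted separately. It is 118 − 29 = 89 if a woman who is still pregnant is not given the birth scale, which the article does not say. On any count, a large share concerns symptoms, trauma or war. The order of the instruments is not given.

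**Where each protection sits.**

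| Stage | What the article describes | Is the help list described there? |
|---|---|---|
| Consent form | Content, risks and benefits, voluntary participation | No |
| Ineligible at the consent form | Thanks, and the requirements for taking part | No, but no questionnaire item has been seen |
| During the questionnaire, about 35 minutes | Nothing | No |
| Leaving before the end | Nothing | No |
| End of survey | List of services and resources | Yes |
| Not stated where or when | Contacts of the national lead research teams | These are not the list |

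**Reading the table.** Women can be exposed to the questions in the third and fourth rows, and the list is described only in the fifth. The consent form informs a woman of risk beforehand, but the article does not say that it directs her to help. The team contacts might be visible during the survey, but they are offered for information, and their placement is left open. So the one measure linked to distress depends on completion.

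**Is stopping early foreseeable?** The Sample size section raises power cuts, evacuation and missiles as obstacles to recruitment. The same conditions can interrupt a session of about 35 minutes. Distress is a second, separate reason to stop.

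**How many women?** The article gives no break-off rate, and none can be derived from the minimum of 300 participants. No count follows from the documents.

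**The case against.** Several points on the other side have force.

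- **Other protections exist.** A reader might infer that the list is the only safeguard and that the risk is otherwise unmitigated. That is too strong. The same paragraph offers research-team contacts, the consent form covers risks before the first question, and the Ethics statement records review and approval by two ethics committees. What stands is narrower: the list is the only measure expressly tied to the distress.
- **Women screened out.** A reader might add those who receive only the thank-you message. The article does not support this. They are stopped at the consent form and have answered nothing, so the distress that the list addresses has not arisen.
- **The list may also appear elsewhere.** The article does not say that the list is shown only on the last page, and a condensed article may omit screen layout. It is therefore too strong to say that a woman who stops can never find it. But the article does state a position, and it is a single one. A protection rule should not depend on a second position that nobody has written down.
- **Who stops, and when.** With no item order given, some women may leave before any sensitive item, and a power cut is not an exit caused by distress. Nothing in the article shows that women who stop are more distressed than those who finish. The point needs only that a distressed woman may be among those who stop.
- **Numbers.** One could assume that 20% to 40% of starters do not finish. That gives 300/(1 − 0.20) − 300 = 75 to 300/(1 − 0.40) − 300 = 200 break-offs per 300 completers. Those rates have no source in the article, and the result counts every break-off for any reason. It does not measure distressed women left without help.
- **Priming.** Showing help contacts early could influence self-reported symptoms, which are the outcomes. An unobtrusive link keeps this effect small.

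**Conclusion.** The concern holds for women who start the questionnaire and stop before the end. For them, the only measure tied to the named risk is not delivered under the rule as written, and the article itself foresees conditions that cause interruption.

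The size is unknown. The conclusion rests on reading the stated position of the list as the full rule, and on at least some women leaving part-way after sensitive items. It does not rest on any particular break-off rate. It does not extend to ineligible women, and it does not mean that the study lacks other protections. This is a low-cost improvement to participant protection. It does not touch the sample size or the planned analyses.

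**What to change.** Amend the Ethical standards text so that the list of services and resources is reachable by an unobtrusive fixed link on every survey page and on any exit or withdrawal page, and stays on the final page as now. If the live survey already does this, one sentence saying so settles the point.

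The cost is a small edit to the survey pages and possibly a notification to the ethics committees. The list must be ready before the first participant starts, which end-of-survey display requires in any case. The remaining downside is at most slight priming of answers.

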### Procedure

Potential participants will be sought out through social media platforms (e.g., Twitter, Facebook, Instagram, LinkedIn, ResearchGate, WhatsApp), networks of educational institutions, healthcare facilities, and non-governmental organizations working in the area of perinatal mental health, policymakers, local organizations, and other stakeholders (utilizing the contacts provided by the Riseup-PPD), in addition to the personal networks of the research team members and through direct contact *via* text or email.

Participants taking part in the study will be asked to click on the website link found on the general project website^1^ in order to access the online questionnaire. They will then be presented with an electronic consent form that outlines the purpose and content of the questions, the risks and benefits, and the ethical considerations (such as voluntary participation, data confidentiality, secure storage of data, and the lack of financial compensation). At the bottom of the form, they must confirm that they meet the eligibility criteria and provide consent for the study. If a participant does not meet the criteria, they will be directed to a message thanking them for their interest and informing them of the requirements for participation. Completion of the baseline questionnaire is estimated to take around 35 min.

### Data analysis

#### Descriptive

At the beginning, descriptive statistics will be examined for all the study variables. To analyze the presence or not of the different variables (depression, anxiety or PTSD) concerning the different categorical variables, contingency tables will be made using *Pearson’s Chi-Square*. *Cramer’s V* will be used to calculate the effect size. Likewise, when the variables are continuous, Student’s *t* will be used, and the effect size will be calculated using Cohen’s *d.*

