Another risk factor for mental health is the individual adaptation to a new life in the host country. Heslehurst et al. (2018) reported daily difficulties faced by immigrants and asylum seekers in the host country: not knowing the language and being unfamiliar with the local lifestyle and health practices can create additional burdens and risks for mental and general health. Systematic reviews report that perinatal outcomes such as mental health, maternal mortality, preterm birth and congenital anomalies are predominantly more severe among migrant women (Falah-Hassani et al., 2015: Heslehurst et al., 2018). In a German study, 87.4% of the pre-and postpartum migrants were affected by medical complications or high-risk pregnancies (Kaufmann et al., 2022). However, these studies often do not distinguish among the different statuses of migrant (refugee vs. immigrant) populations, and host countries that may significantly differ regarding the organization of access to support and health care services. For example, an Australian study (Snow et al., 2021) showed elevated psychosocial risk factors among women of refugee background compared with Australia born-women, with the possible under-reporting of mental health problems and family violence. Research on healthcare for pre-, peri- and postpartum refugee women in high-income countries has shown that their access to health care is hampered by immigration experiences, insufficient health literacy, poor language skills, insufficient perception of health needs and use of health services, and legal restrictions (Haith-Cooper and Bradshaw, 2013; Rizkalla et al., 2020). These results raise questions regarding assessing psychosocial risk within different cultural groups and show the importance of the culture-sensitive approach to women with different cultural backgrounds. A systematic review and meta-analysis showed that the prevalence of current PTSD among migrants exposed to armed conflict is 31%, the current major depressive disorder is 25%, and the prevalence of generalized anxiety disorder is 14% (Mesa-Vieira et al., 2022). Migrating to a middle-income or low-income country was associated with an increased prevalence of generalized anxiety disorder—however, evidence is still scarce (Fellmeth et al., 2018).

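### Student's t is named for comparing women with and without depression, anxiety or PTSD; those groups are likely to be unequal in size, so Welch's t would be the safer test (minor)

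*Protocol article*

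**What the plan says.** The Descriptive part of the Data analysis section opens with "At the beginning, descriptive statistics will be examined for all the study variables". It then sets up a comparison by outcome status: "To analyze the presence or not of the different variables (depression, anxiety or PTSD) concerning the different categorical variables" will be examined with contingency tables, Pearson's chi-square and Cramer's V. For continuous variables the next sentence reads: "Likewise, when the variables are continuous, Student’s *t* will be used", with Cohen's d as the effect size. The opening word of that sentence carries over the same grouping, women with and without the condition. This is the natural reading, though it is not spelled out. No unequal-variance form and no handling of unequal variances is mentioned, and no confidence interval is planned for these mean differences.

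The Sample size section fixes the total: "a minimum sample size of 300 individuals will be recruited using a significance level of α-level of 0.05 and variability of 50" per cent. The article gives no SD for any variable and no expected number of cases.

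**The concern.** The pooled-variance test estimates one common SD, in which the larger group carries most of the weight. If the smaller group is more variable, the standard error is too small and the test rejects too often. If the smaller group is less variable, the standard error is too large and the test rejects too rarely. With equal group sizes the two effects cancel.

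Groups formed by case status have no reason to be equal in size. The Introduction cites case shares well below one half: "the prevalence of current PTSD among migrants exposed to armed conflict is 31%, the current major depressive disorder is 25" per cent, and 14% for generalised anxiety disorder. At stake are the p-values attached to continuous variables in the case versus non-case tables. They would depend on an equal-SD assumption that nothing in the design protects. Cohen's d has a related gap: when SDs differ, its value depends on which SD is the divisor, and the article does not say.

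**Working it through.** **Inputs**
- Total n = 300 (Sample size section). This is the only computed figure in the article and is taken as given. It cannot be reproduced uniquely because no margin of error is stated; it matches 1.96 × √(0.25/300) = 5.66 percentage points. This does not bear on the point.
- Case shares (Introduction): 14% anxiety, 25% depression and 31% PTSD in migrants exposed to armed conflict; 28.2% of women at high risk of postpartum depression in war-affected Syria; 34.8% PTSD in internally displaced pregnant women. A share of 50% is added for comparison.
- Alpha 0.05, assumed two-sided.
- Ratio r of case SD to non-case SD: not in the article. Assumed, 0.67 to 2, with the non-case SD set to 1.

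**Group sizes** (n₁ cases, n₂ non-cases): 300 × 0.14 = 42 v 258; 300 × 0.25 = 75 v 225; 300 × 0.282 ≈ 85 v 215; 300 × 0.31 = 93 v 207; 300 × 0.348 ≈ 104 v 196.

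**Formulas**
- True variance of the mean difference: V = r²/n₁ + 1/n₂
- Variance the pooled test uses: Vp = [((n₁−1)r² + (n₂−1))/298] × (1/n₁ + 1/n₂)
- Standard error ratio k = √(Vp/V); approximate true error = 2 × [1 − Φ(1.968 × k)]

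**Example, 42 v 258, r = 1.25**
- V = 1.5625/42 + 1/258 = 0.04108
- Vp = (41 × 1.5625 + 257)/298 × (1/42 + 1/258) = 1.0774 × 0.02769 = 0.02983
- k = √(0.02983/0.04108) = 0.852; error = 2 × [1 − Φ(1.677)] = 9.4%

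**Example, 104 v 196, r = 1.25**: V = 0.02013, Vp = 0.01758, k = 0.935, error = 6.6%.

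**Simulated error of the pooled test when the means are equal** (normal data, 40,000 runs per cell, in %):

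| Case share | Groups | r = 0.67 | 0.8 | 1 | 1.25 | 1.5 | 2 |
|---|---|---|---|---|---|---|---|
| 14% | 42 v 258 | 0.9 | 2.2 | 5.1 | 9.5 | 14.2 | 21.5 |
| 25% | 75 v 225 | 1.7 | 2.9 | 5.0 | 7.9 | 10.9 | 15.3 |
| 28.2% | 85 v 215 | 2.0 | 3.1 | 4.9 | 7.7 | 9.8 | 13.5 |
| 31% | 93 v 207 | 2.3 | 3.5 | 5.0 | 7.1 | 9.0 | 11.9 |
| 34.8% | 104 v 196 | 2.8 | 3.5 | 4.8 | 6.8 | 7.9 | 10.5 |
| 50% | 150 v 150 | 5.1 | 5.0 | 5.2 | 5.0 | 5.1 | 5.1 |

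Welch's test stays between 4.8% and 5.2% in every cell. The column r = 1 shows that unequal group sizes alone do no harm.

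**Power cost of Welch's test when SDs are equal** (simulated, at 50% to 90% power): 0.9 to 1.2 percentage points at 42 v 258, about 0.3 at 75 v 225, and 0.2 or less at 93 v 207 and 104 v 196.

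**Cohen's d**, 42 v 258, r = 1.25, illustrative mean difference of 0.5 non-case SDs: d = 0.5/1 = 0.50 with the non-case SD, 0.5/1.038 = 0.48 with the pooled SD, 0.5/1.132 = 0.44 with the root mean square of the two SDs, and 0.5/1.25 = 0.40 with the case SD.

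**The case against.** The best case against is that this is a conditional remark about a descriptive step. Most of its parts stand and limit the point.

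- Harm needs unequal SDs as well as unequal sizes, and the article gives no SDs. This stands.
- A variable wholly unrelated to case status has the same distribution, and so the same SD, in both groups, and Student's t then holds its 5%. This also stands. A reader might infer that pure noise variables would be declared risk factors at 10% or 20%; the calculation does not show that. It shows the error for variables with equal means but different spread. Where the means do differ, the misstated standard error still distorts the p-value.
- A reader might infer that the groups are bound to be very unequal. The article does not say so. The cited rates come from other populations, only the 14% figure gives about 1:6, and the others give roughly 1:2 to 1:3. Shares at the study's EPDS, GAD-7 and IES-R cut-offs are unknown, and near 50% the problem vanishes.
- A reader might infer that confidence intervals or the main risk-factor findings are at risk. No interval is planned for these tests, and the prediction and logistic models do not rest on them.
- A reader might extend the point to internal versus external refugees. The Descriptive text names no such comparison, and that split is unknown.
- Equal variances are not written into the text, and a condensed article may leave variance handling to a fuller plan. This stands only in part: the article does not leave the test open. It names one, and the ordinary meaning of that name is the pooled test.

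**Conclusion.** The point holds as a minor one. The article names a test that, in its ordinary form, is sensitive to unequal SDs at the group splits its own cited rates suggest. For a case to non-case SD ratio of 1.25 the nominal 5% becomes about 7% to 9%; for a ratio of 0.8 it becomes about 2% to 4%; with equal SDs or equal groups it stays at 5%. The larger errors in the table need SD ratios of 1.5 or more and should not be read as expected values.

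This rests on four assumptions: that the case versus non-case grouping applies to the t test, that n is about 300, that the case shares resemble the cited ones, and that SDs differ. The last two cannot be settled from the article. The consequence is confined to the descriptive group comparisons.

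**What to change.** In the Descriptive part of the Data analysis section, replace Student's t with Welch's unequal-variance t test for the two-group comparisons of continuous variables. In the same sentence, state which SD is the divisor in Cohen's d.

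The cost is one line of wording and, if the variances are in fact equal, a power loss of about 1 percentage point at the most unequal split considered and less at the others. No other part of the analysis needs to change.

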#### Psychometric properties

To examine the psychometric properties of the questionnaires in the Ukrainian language, several analyses will be reported. Exploratory Factor Analyses (EFA) will be conducted using Statistical Package for the Social Sciences (SPSS), Version 26 software. Analysis of the factor dimensional constraints will determine each model’s underlying individual item loadings. Based on the results of the EFA, Confirmatory Factor Analysis (CFA) will then be analyzed. ECA will be used to analyze how to fit the models using several indexes such as Satorra-Bentler χ^2^, CFI, RMSEA and the confidence interval of RMSEA statistics will be calculated. Lagrange multipliers and Wald test will be sequentially performed to improve the models’ fitness, following the study’s hypotheses. Standardized coefficients and measurement equations with scores in R2 will be reported. These analyses will be conducted using the AMOS program.

Prediction models. To examine the risk and protective factors associated with perinatal mental health outcomes, a random sample of 70% of participants will be used to derive the machine learning algorithms, including regularized logistic regression, random forest, decision tree, and gradient boosting to predict the risk of perinatal mental health outcomes, and their performance, and the remaining 30% for validation. First, in the derivation sample, all predictors described above will be included in the models to estimate the probability of depression, anxiety, or PTSD. Beginning with a model containing all potential covariates, the variable with the least significant *p* value will be removed and tested using the likelihood-ratio test until all variables left in the model significantly (at alpha = 0.05) contributed to the model.

In regularized logistic regression models, results will be presented as Odds Ratio (OR) with 95% confidence intervals (CIs).

Logistic regression analyses will be conducted using the steps forward procedure to examine which variables will predict the study’s dependent variables. This regression analysis makes it possible to predict a dichotomous dependent variable based on predictor, categorical or quantitative variables the R^2^ will be used to calculate the proportion of the explained variance of clinical outcomes by the selected predictors. The different aspects of model performance will be studied. The receiver operating characteristics (ROC) curves (and the corresponding area under the ROC curve—AUC) will also be calculated to test for discrimination characteristics.

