### Experience during the birth: City BIRTH

The City Birth Questionnaire (Ayers et al., 2018) evaluates PTSD symptoms within the context of childbirth and it contains 29 items related to the DSM-5 diagnostic criteria. It also has two other remaining questions related to the DSM-IV diagnostic criteria. This questionnaire examines participant’s subjective feelings of discomfort related to a specific traumatic event. The City Birth Trauma Scale assesses two factors, Birth-related symptoms and General symptoms of re-experiencing the traumatic event (Ayers et al., 2018; Nakić Radoš et al., 2020). The scores range from 0 to 60. As the authors have pointed out, the scores for percentiles are 25th = 3, 50th = 9, 75th = 18. The questionnaire has shown good psychometric properties (Ayers et al., 2018; Nakić Radoš et al., 2020).

The Ukrainian version, “Міська шкала пологової травми” was translated for the purpose of the study by the authors.

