### Impact of events scale-revised

The Impact of Event Scale-Revised (IES-R; Weiss and Marmar, 1997) is a self-assessment tool measure for capturing the level of symptomatic response to specific traumatic stressors as it was manifested in the previous 7 days.

The scale has been translated into different languages (Baguena et al., 2001; Asukai et al., 2002) and different samples (Beck et al., 2008) with good psychometric properties.

A revised version of the Impact of Event Scale-Revised by Weiss and Marmar (1997), contains 22 items with scores gathered using a 5-point scale (0–4). What differentiates this revised version of the Impact of Event Scale (IES-R) from the previous one is that this latest version has seven additional questions and a scoring range of 0 to 88.

On this test, a score of 24 or more is clinically significant as it is indicative of an individual having full or partial PTSD. A score of 33 or more is the most accurate way to determine the probability of PTSD, and a score of 37 or higher is a strong indication of the disorder (Weiss, 2007).

This questionnaire considers the three dimensions of PTSD according to DSM-IV (Weiss and Marmar, 1997), including the following: Intruding recurring images, dreams, and/or thoughts or perceptual impressions related to the traumatic event; Agitation characterized by increased alertness, anxiety, impatience, and/or difficulty concentrating attention; and Avoidance manifested by efforts to get rid of thoughts, emotions, or conversations related to the traumatic event.

The Ukrainian version “Шкала впливу стресових подій – переглянута (ШВСП-П)” was translated into Ukrainian by the study authors.

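### The CFA model is taken from the EFA and then modified to improve fit with no independent sample named, so its final fit indices will be optimistic and are not confirmatory evidence for the Ukrainian scales

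*Protocol article*

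**What the plan says.** The protocol article, under Data analysis, Psychometric properties, sets three ordered steps for the questionnaires in Ukrainian.

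1. Exploration: "Exploratory Factor Analyses (EFA) will be conducted using Statistical Package for the Social Sciences (SPSS), Version 26 software".
2. Confirmation of what was explored: "Based on the results of the EFA, Confirmatory Factor Analysis (CFA) will then be analyzed". Fit is judged by "several indexes such as Satorra-Bentler χ^2^, CFI, RMSEA and the confidence interval of RMSEA statistics will be calculated".
3. Modification: "Lagrange multipliers and Wald test will be sequentially performed to improve the models’ fitness, following the study’s hypotheses".

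No subsample, hold-out or second sample is named for any of these steps. Later in the same section a split is described, but for the prediction models: "a random sample of 70% of participants will be used to derive the machine learning algorithms", with the remaining 30% for validation. The Sample size section plans one sample of at least 300.

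The measure descriptions cite prior structures for two scales. For the IES-R: "This questionnaire considers the three dimensions of PTSD according to DSM-IV". For the City BiTS: "The City Birth Trauma Scale assesses two factors, Birth-related symptoms and General symptoms". Neither is named as the model that the CFA will test. The sections on the EPDS and GAD-7 give no factor structure.

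**The concern.** A CFA is informative when the model is fixed before the data are seen. Here the model comes from the data by way of the EFA, and is then adjusted on fit. Fit indices computed after such a search describe how well the model was tuned to this sample. They tend to be better than the same model would show in other women.

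This matters because the evidence is otherwise thin. The study team translated the EPDS, IES-R and City BiTS, and the GAD-7 section says that the Ukrainian version has no psychometric study yet. The first main goal includes the proportion of women above a cut-off on a validated scale. The factor analyses are the only Ukrainian validity evidence that the article plans for these four symptom scales. If tuned fit is reported as confirmation, that evidence is overstated. The direct question for a translation, whether it reproduces the structure known from other languages, is not set as a test.

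**Working it through.** The plan states no sample size or fit target for the factor analyses, so there is no figure of its own to reproduce. Two checks show where the optimism arises and roughly how large it is.

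**1. Room for chance modification.** A scale with p items has m = p(p − 1)/2 possible residual covariances. If the model is correct, about 0.05 × m of the single-parameter Lagrange tests exceed 3.84 by chance.

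| Scale | Items | m | 0.05 × m |
|---|---|---|---|
| EPDS | 10 (article) | 10 × 9/2 = 45 | 2.25 |
| IES-R | 22 (article) | 22 × 21/2 = 231 | 11.55 |
| City BiTS | 20 (assumed) | 20 × 19/2 = 190 | 9.5 |

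The 20 City BiTS items are an assumption: the article gives 29 items and a 0–60 range, and 20 scored items follow only if each is scored 0–3. For the EPDS, if the tests were independent, the chance of at least one false signal is 1 − 0.95^45 = 0.90. These counts show how many chance candidates a search could meet. They do not predict how many parameters would be freed.

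**2. Illustrative simulation of the sequence.** The assumptions are not from the article:
- ten continuous normal items on two factors correlated 0.6, with main loadings 0.55–0.70, small random cross-loadings and minor factors, so that the simple model is somewhat wrong;
- a two-factor EFA, with each item assigned to its strongest factor, then a maximum-likelihood CFA in the same sample;
- up to three residual covariances added by an approximate Lagrange test above 3.84 (no Wald step);
- the same model form refitted in an independent sample of equal size.

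Means over 300 replicates (n = 300) and 298 replicates (n = 150):

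| n | Model | CFI, same sample | CFI, independent | RMSEA, same sample | RMSEA, independent |
|---|---|---|---|---|---|
| 300 | EFA-derived, unmodified | 0.857 | 0.856 | 0.111 | 0.110 |
| 300 | after modification | 0.929 | 0.908 | 0.081 | 0.092 |
| 150 | EFA-derived, unmodified | 0.852 | 0.841 | 0.113 | 0.116 |
| 150 | after modification | 0.935 | 0.890 | 0.076 | 0.101 |

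At n = 300, using the EFA sample again for the CFA adds almost nothing: 0.857 − 0.856 = 0.001 in CFI. Modification adds 0.929 − 0.908 = 0.021 in CFI and 0.092 − 0.081 = 0.011 in RMSEA. At n = 150 the gaps after modification are 0.935 − 0.890 = 0.045 and 0.101 − 0.076 = 0.025.

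The share of modified models reaching CFI ≥ 0.95 falls from 31% to 13% at n = 300, and from 38% to 11% at n = 150. The share reaching RMSEA ≤ 0.06 at n = 300 falls from 16% to 7%.

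**The case against.** **The article never says that the EFA and CFA use the same women.** True. It is an inference from one described sample and from a split reserved for the prediction models. A fuller protocol could divide the sample. The procedure that the article does fix would remain: a CFA model taken from the EFA, then modified to improve fit. Even with a split, modifications chosen in the CFA part would need a further check.

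**The modifications are limited by the study's hypotheses.** The clause is there and should be read with the rest, since it makes this something other than an unrestricted search. It gives little protection, because no measurement hypothesis is stated. It also leaves open that the cited structures might guide the models; the article is silent on that.

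**A reader might infer that such a CFA can never fail.** The simulation does not support this. After modification at n = 300, 69% of models still missed CFI ≥ 0.95 and 84% missed RMSEA ≤ 0.06. The effect is moderate optimism.

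**A reader might infer that the published cut-offs become unusable.** This does not follow. The cut-offs given for the EPDS, GAD-7 and IES-R apply to total scores. Freeing a residual covariance leaves a total score unchanged, and nothing in the article says that the factor analyses will alter scoring. For the City BiTS only percentiles are given.

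**Wald tests drop parameters and do not lower the chi-square by chance.** This stands; the optimism comes from the Lagrange step.

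**Psychometric validation is not one of the five main goals.** Also true, and it limits the weight of the point. Goal 1 nevertheless relies on the scales being validated.

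**Conclusion.** The point holds. The article fixes a sequence in which the CFA model is derived from the EFA and then modified to improve fit. It names no independent sample for these steps and no measurement hypothesis to bound them. The final fit indices will be optimistic and should not be presented as confirmatory validation of the Ukrainian versions.

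The modification step is the main source. Under the simulation's assumptions the optimism is about 0.02 in CFI and 0.01 in RMSEA at n = 300, and roughly twice that at n = 150. The size depends on assumed loadings, continuous items, an approximate Lagrange test and a limit of three additions; the direction does not. The conclusion also assumes that no split exists in a fuller document. It concerns the strength of the validity evidence. Sum scores and cut-offs are not themselves changed.

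**What to change.** Reverse the order.

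- **First, a CFA of a prespecified structure for each scale, in the full applicable sample, with its fit reported unmodified.** For the IES-R use the cited three dimensions. For the City BiTS use the cited two factors, in women who have given birth. For the EPDS and GAD-7 the article gives no structure, so one should be prespecified.
- **Then any EFA-derived or Lagrange/Wald-modified model, labelled exploratory** and reported beside the unmodified fit, with the changes listed.
- **If a modified model is to be proposed for use,** assess it by cross-validation or in a held-out part of the sample.

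This changes analysis wording and needs no new data. The fit indices may look less favourable. A held-out half of 300 leaves about 150 women, and fewer for the City BiTS, while the Sample size section warns that even 300 may be hard to reach. Cross-validation, or plain exploratory labelling, is therefore the cheaper option.
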